## Results

The study was approved by the Research Ethics Committee of Universiti Kebangsaan Malaysia for implementation from January 27, 2020, to July 26, 2026. The sponsor successfully disbursed funding in June 2020. Participant screening, recruitment, and data collection commenced in September 2020. As of April 2025, 339 participants were screened, with 211 recruited and 167 having completed the study. Data analysis was completed for the first 120 participants, evenly divided between the placebo and TRF supplementation groups. Final results are expected to be published in 2026, following the completion of data collection and unblinding of the IPs by the sponsor.

## Discussion

This study was conducted to evaluate the effectiveness of TRF (DavosLife E3 Complete) on blood biochemical composition (liver function, lipid profile, renal function, full blood count, and fasting glucose), oxidative status biomarkers (MDA, AGE, F2-IsoPs, and PC), inflammation biomarkers (TNF-α and IL6), appetite regulation biomarkers (leptin and ghrelin), arterial stiffness, skin health, bone density, and cognitive function in healthy older adults aged 50 years to 75 years over a 6-month intervention period. We hypothesized that the high antioxidant and anti-inflammatory properties of TRF would result in significant improvements across several different areas, particularly vascular function and cognitive performance. In order to provide more thorough knowledge on the role of TRF in promoting healthy aging, skin and bone parameters were also included to investigate the potential benefits of TRF on structural and aesthetic elements of aging. The goal of this study is to meet the increasing need for a safe, nonpharmacological intervention that can help the older population maintain their functional lifespan, quality of life, and physiological resilience.

The 5-year clinical trial was designed in accordance with the SPIRIT (Standard Protocol Items: Recommendations for Interventional Trials) guidelines and registered in the National Medical Research Register of Malaysia. Prior to the initiation of the trial, the investigators and sponsor signed a mutual confidentiality agreement. This agreement serves to safeguard against any unauthorized use, disclosure, publication, or dissemination of confidential information by both parties involved. Separately, a comprehensive research agreement was signed, addressing the roles of the investigators and sponsor, ownership of liabilities, indemnification and insurance, quality assurance, record-keeping, reporting, access, intellectual property, and publication and authorship.

The trial commenced in 2019 after ethical approval was obtained. Notably, although sponsored by a commercial company, the trial is conducted entirely by the institution independently of the sponsors. Participant recruitment, sampling, and analyses are performed by the investigators who are blinded to the participants’ identification to prevent bias. Volunteers undergo random screening and are recruited based on their fulfillment of the inclusion criteria. Similarly, the administration of investigational products is also randomized.

On average, the screening process typically lasts around 2 hours. According to the latest data, approximately 60% of the volunteers successfully met the inclusion criteria and became eligible for recruitment into the study. The primary reasons for volunteer exclusions were elevated levels of total cholesterol, low-density lipoprotein cholesterol, fasting blood glucose, and blood pressure. On average, each participant requires approximately 3 hours to complete all assessments, excluding blood tests. To accommodate the fasting requirement for blood withdrawal and arterial stiffness assessment, these tests are conducted first. Subsequently, the remaining assessments are performed simultaneously at different stations, allowing participants to visit any available station. To minimize the waiting time, a maximum of 5 participants are scheduled per sampling day. This ensures that participants do not experience prolonged waiting periods.

Throughout the treatment period, the research assistants monitor the compliance of the participants through regular phone calls and short messages. However, the effectiveness of this monitoring method relies on the participants’ availability to respond to or read the messages. Noncompliant cases were primarily attributed to participants’ difficulty with remembering to take the supplement, which is evident when they return the bottles with a higher number of remaining softgels than expected during the 3- and 6-month visits. The data from noncompliant participants are still analyzed. However, it is specifically noted in the CRF so that any potential outliers in data analysis can be identified later.

The findings of this study will further extend our current knowledge in many ways. As the older adult population continues to increase globally [103], understanding the efficacy of TRF supplementation for promoting healthy aging becomes increasingly imperative. The use of a randomized, double-blind, placebo-controlled study protocol to assess the effectiveness of TRF in older adults offers numerous advantages that significantly enhance the credibility and reliability of the research findings. First, the randomization process ensures an unbiased allocation of participants into the treatment and control groups, minimizing the influence of confounding variables and increasing the validity of the study results. Second, the double-blinded nature of the trial eliminates both participant and researcher bias, as neither knows who is receiving the active intervention or the placebo, thereby preventing any preconceived notions from influencing outcomes. This rigorous blinding protocol ensures the integrity of the data collected and provides a more accurate assessment of the true effects of TRF supplementation. Finally, the inclusion of a placebo group enables researchers to distinguish between the specific effects of TRF and any placebo effects, ensuring that observed improvements in health outcomes can be confidently attributed to the intervention. Overall, by adhering to such a meticulous study protocol, researchers can generate robust evidence regarding the efficacy of TRF for promoting health and well-being among older adults, ultimately informing clinical practice and guiding future research endeavors.

There are some possible limitations of this study. One significant limitation is the potential for dropout or noncompliance among older participants, which can compromise the integrity of the study results and introduce bias. Older adults may face unique challenges such as cognitive impairment, mobility issues, or comorbidities that affect their ability to consistently adhere to the study protocol. Moreover, the relatively long duration often required for such trials increases the likelihood of attrition over time. Additionally, the strict inclusion and exclusion criteria necessary to ensure the internal validity of the study may limit the generalizability of the findings to broader older adult populations with diverse characteristics and health profiles [104]. Thus, researchers must remain cognizant of these limitations and use strategies to mitigate their impact on the study outcomes.

In conclusion, our study holds immense promise for advancing our understanding of the potential health benefits of TRF. While acknowledging the inherent challenges and limitations associated with conducting trials in older adult populations, the insights gleaned from this study have the potential to significantly impact clinical practice. Ultimately, by generating robust evidence regarding the efficacy of TRF supplementation for promoting healthy aging, this study protocol has the potential to contribute valuable insights to the field of geriatric medicine, paving the way for improved strategies to enhance the quality of life and well-being of older adults worldwide.

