### Recruitment

The selection of potential trial participants is conducted by the PI based on the inclusion and exclusion criteria. Participants who fail to meet the inclusion and exclusion criteria are defined as screening failures. The PI maintains a Screening Log, which includes screen failures to ensure a systematic selection of participants. Informed consent is obtained from each participant by the contract research assistants. During enrollment, general information (name, gender, age, address, and contact information) is obtained. To ensure security and confidentiality, each participant is assigned a participant-specific code. The code is used to label the participant’s laboratory results. Each participant is reimbursed for standard transportation fees.

Participants are free to withdraw from the study at any time for any reason. Participants may also be withdrawn at any time at the discretion of the PI. Possible reasons for withdrawal include abnormal laboratory values, protocol violation, the participant requiring the use of an unacceptable concomitant medication, participant not complying with protocol procedures, participant developing a condition during the study that violates the inclusion or exclusion criteria, loss to follow-up, death, or any other reason in the PI’s opinion that would impede participation in the study.

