All randomized participants are included in the primary analysis using the intention-to-treat approach, which analyzes participants based on their initial group allocation regardless of whether they adhere to the intervention. Only participants who complete the study without significant protocol deviations are included in a secondary per-protocol analysis.

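### Discretionary withdrawal and replacement of non-compliers is not reconciled with the intention-to-treat commitment, so behaviour after randomization can cost later outcome data

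*Protocol article*

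**What the plan says.** All references are to the protocol article.

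- **Recruitment.** "Participants may also be withdrawn at any time at the discretion of the PI". Among the possible reasons is "participant not complying with protocol procedures". No threshold is given, and nothing is said about assessments after withdrawal.
- **Analyses, on replacement.** When someone withdraws or is eliminated, the ID number is retired, a new volunteer is recruited so that the total stays at 220, and product numbers are re-randomized and adjusted to keep 110 per product.
- **Analyses, on analysis sets.** "All randomized participants are included in the primary analysis using the intention-to-treat approach", and this approach "analyzes participants based on their initial group allocation regardless of whether they adhere to the intervention". Deviations matter only for a further set: "Only participants who complete the study without significant protocol deviations are included in a secondary per-protocol analysis".
- **Monitoring.** Compliance percentage enters the statistical analyses as a covariate, and subgroups by high, medium and low compliance are planned. The covariate is not limited to secondary analyses.
- **Discussion.** Non-compliance, mainly forgetting the supplement, is seen from the bottles returned at months 3 and 6. "The data from noncompliant participants are still analyzed". The text then says of non-compliance that "it is specifically noted in the CRF so that any potential outliers in data analysis can be identified later".

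**The concern.** Intention-to-treat needs more than a definition of the analysis set: outcomes must still be collected from people who stop complying. Here adherence, which is observed after randomization, can trigger withdrawal at the PI's discretion and then replacement. Two participants with the same leftover softgel count could be treated differently, one withdrawn and replaced, the other kept and flagged. The Analyses section requires both in the primary comparison.

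Replacement restores the head count but not comparability, because the newcomer does not stand in for the outcome of the person who left. If every randomized participant stays in the set, the set will exceed 220 once anyone is replaced. The text does not say whether 220 counts those randomized or those retained.

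Non-compliance may also be related to outcome. The Discussion names cognitive impairment and comorbidities as threats to adherence, and cognition is itself an outcome of the trial.

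**Working it through.** **1. What withdrawal loses, by endpoint.** Table 1, the Outcomes section and the Discussion fix the visits. (The Participant Timeline section lists all domains together under three visits; the more specific schedule is used here.)

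| Endpoints | Visits (months) | Withdrawn after month 3 | Withdrawn before month 3 |
|---|---|---|---|
| Blood biochemistry, oxidative stress, inflammation, appetite, skin | 0, 3, 6 | month 3 value remains | baseline only |
| Arterial stiffness (primary), cognition, bone density (secondary) | 0, 6 | baseline only | baseline only |

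For the second row, any withdrawal before month 6 leaves no post-baseline value.

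**2. What the missing-data plan can do.** The Analyses section names mixed models under missing at random, with pattern-mixture and delta-adjusted imputation as sensitivity analyses. For a participant with baseline only, the mixed model has nothing on response and relies on those who stayed. The sensitivity analyses show how conclusions move under assumed departures. Neither recovers an outcome that was never collected. The mixed-design ANOVA in the same section ordinarily uses complete rows only.

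**3. Rates.** None are given. The Results section reports 211 recruited and 167 completed, so 211 − 167 = 44 had not completed. These may be in follow-up or withdrawn; the text does not separate them.

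**4. Illustrative size, assuming no treatment effect.** Suppose shares p(TRF) and p(placebo) are lost from the analysis, and those lost have worse outcomes than those kept by a gap g, the same in both arms.

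- Bias = (p(TRF) − p(placebo)) × g.
- Planned effect for scale (Sample Size section): (3.11 − 2.66) / sqrt((0.81² + 1.25²)/2) = 0.45/1.053 = 0.427 SD.
- Standard error with 88 per arm (110 × 0.8) and an assumed baseline correlation r = 0.7: sqrt((1 − 0.49) × 2/88) = sqrt(0.51 × 2/88) = 0.108 SD.
- Two-sided error = Φ(−1.96 + bias/SE) + Φ(−1.96 − bias/SE).
- If the gap is already present at baseline and stable, baseline adjustment leaves g × (1 − r) = 0.3g.

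| Lost, TRF / placebo | g (SD) | Bias, gap wholly after baseline | Error | Bias, gap stable from baseline | Error |
|---|---|---|---|---|---|
| 20% / 10% | 0.3 | 0.10 × 0.3 = 0.03 | 5.9% | 0.009 | 5.1% |
| 25% / 10% | 0.4 | 0.15 × 0.4 = 0.06 | 8.6% | 0.018 | 5.3% |
| 30% / 10% | 0.5 | 0.20 × 0.5 = 0.10 | 15.3% | 0.03 | 5.9% |
| equal shares, same g | any | 0 | 5% | 0 | 5% |

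Against 0.427 SD, the bias runs from 0.009/0.427 = 2% to 0.10/0.427 = 23%. Loss shares, gaps and r are all assumptions. The calculation also treats lost participants as absent, with no help from the mixed model.

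**5. The compliance covariate.** Compliance is measured after randomization. Adjusting the main comparison for it no longer estimates the effect of allocation regardless of adherence, which is what the Analyses section promises.

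**The case against.** The strongest reply is that the passages can coexist. Withdrawal is optional, and withdrawal from the study is not removal from the analysis set. The Recruitment wording concerns protocol procedures in general, whereas the non-compliers in the Discussion forgot softgels, still attended visits and are expressly analyzed. The article also has a reasonable missing-data plan. All of this stands, so the passages are unreconciled rather than flatly contradictory. It does not supply the missing statement that follow-up continues, or settle the status of a withdrawn participant who has been replaced.

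Two stronger readings are tempting.

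- A reader might infer from the CRF flag that non-compliers' values will be discarded as outliers, turning the intention-to-treat result into something near per-protocol. The text does not support this. The sentence just before the flag says their data are analyzed, the flag only identifies, and deviation-based exclusion is confined to the secondary set. A detailed outlier rule may also sit in an analysis plan that is not shown. The fair criticism is that the article ties outlier review to adherence without saying what follows.
- A reader might infer that a withdrawn participant has no outcome at all. That is wrong for endpoints measured at month 3 when withdrawal comes later.

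Unequal loss between arms is also not established. The softgels are odorless and alike, the bottles are opaque, and the main stated cause of non-compliance is forgetting.

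**Conclusion.** The point holds in a limited form. The article allows non-compliance to end participation and trigger replacement, without saying that outcomes are still collected or that the withdrawn participant stays in the intention-to-treat set. The loss is complete for arterial stiffness, cognition and bone density when withdrawal precedes month 6, and partial for the endpoints with a month 3 visit.

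The size cannot be taken from the documents. Over the scenarios shown, bias is about 0.01 to 0.10 SD. The 15.3% error rate should not be read as an expected figure: it needs a 30% versus 10% loss and a 0.5 SD gap arising wholly after baseline. With a gap stable from baseline, the same scenarios give 5.1% to 5.9%. The bias favours TRF only if more TRF than placebo participants are lost and those lost do worse. If adherence and its relation to outcome are the same in both arms, only information is lost.

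The change is worth making because it is cheap and the Results section places unblinding still ahead.

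**What to change.** - **Recruitment and Analyses (replacement).** State that non-compliance alone does not end data collection, and that month 3 and 6 assessments are still sought, subject to consent. State that withdrawn participants stay in the intention-to-treat set with their observed data, that replacements are added and do not displace them, and what 220 counts.
- **Discussion.** State that no value leaves the intention-to-treat analysis because of non-compliance. Limit outlier queries to documented measurement or transcription error, made without sight of compliance or product number.
- **Monitoring.** Confine the compliance covariate and the adherence subgroups to supplementary analyses.

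These changes concern data collection and analysis only. Any decision to stop the product on clinical grounds stays as the protocol has it.

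The cost is wording in four places, matching CRF guidance, a few extra attended visits and slightly more analysis work. Participants already withdrawn should be listed, with whatever data were observed, before unblinding.

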## Appendix

Multimedia Appendix 1 SPIRIT (Standard Protocol Items: Recommendations for Interventional Trials) checklist.

## Abbreviations

αTP: alpha tocopherol
AGE: advanced glycation end product
CRF: case report form
CRP: C-reactive protein
DEXA: dual-energy X-ray absorptiometry
F2-IsoPs: F2-isoprostanes
IL-6: interleukin-6
IP: intervention product
MDA: malondialdehyde
MoCA: Montreal Cognitive Assessment
NF-κB: nuclear factor kappa B
PC: protein carbonyl
PI: principal investigator
RAVLT: Rey Auditory Verbal Learning Test
RONS: reactive oxygen and nitrogen species
SPIRIT: Standard Protocol Items: Recommendations for Interventional Trials
STAT-3: signal transducer and activator of the transcription-3
TNF-α: tumor necrosis factor α
TRF: tocotrienol-rich fraction
